## Abstract

**Background:**

The prevalence of childhood obesity among adolescents has been rapidly rising in Mainland China in recent decades, especially in urban and rich areas. There is an urgent need to develop effective interventions to prevent childhood obesity. Limited data regarding adolescent overweight prevention in China are available. Thus, we developed a school-based intervention with the aim of reducing excess body weight in children. This report described the study design.

**Methods/design:**

We designed a cluster randomized controlled trial in 8 randomly selected urban primary schools between May 2010 and December 2013. Each school was randomly assigned to either the intervention or control group (four schools in each group). Participants were the 4^th^ graders in each participating school. The multi-component program was implemented within the intervention group, while students in the control group followed their usual health and physical education curriculum with no additional intervention program. The intervention consisted of four components: a) classroom curriculum, (including physical education and healthy diet education), b) school environment support, c) family involvement, and d) fun programs/events. The primary study outcome was body composition, and secondary outcomes were behaviour and behavioural determinants.

**Discussion:**

The intervention was designed with due consideration of Chinese cultural and familial tradition, social convention, and current primary education and exam system in Mainland China. We did our best to gain good support from educational authorities, school administrators, teachers and parents, and to integrate intervention components into schools’ regular academic programs. The results of and lesson learned from this study will help guide future school-based childhood obesity prevention programs in Mainland China.

**Trial registration:**

Registration number: ChiCTR-ERC-11001819

## Background

Childhood obesity has become a global epidemic [1]. China is one of many countries to be dramatically affected by this growing epidemic in recent years [2,3]. Obesity has many serious health and financial consequences [4-6]. Excess body weight during adolescence not only predicts adult obesity but also influences morbidity and mortality in adult life [7]. Treating obesity is both difficult and costly [8]. The obesity epidemic demands urgent population-based research on childhood obesity prevention programs to determine which programmes are effective and sustainable.

Schools are critical settings for promoting lifelong healthy eating and physical activity (HEPA) [9,10], and for preventing childhood obesity [10,11]. Several systematic reviews [12-15] and some recent studies [16-19] have shown that school-based prevention of obesity is feasible and effective; however other studies have not shown significant effects [20-22]. Although these school-based intervention studies have generally focused on improving healthy eating behavior and the promotion of physical activity (PA), different strategic components and follow-up periods make it difficult to compare the study results. Moreover, most of these studies were conducted in Western countries, and results from Western countries may not be directly applicable to the Chinese population, given obvious differences in school activities and structures between Western and Chinese societies (e.g., Chinese school students spend much more time in academic study) [23]. Hence, there is a need for a well-designed school-based intervention programme for obesity prevention in Chinese population.

To date, only four studies have investigated obesity prevention among school children in Mainland China, three in the language of Chinese and one in English [24-27]. These studies implemented individualized interventions focusing on controlling body weight in obese children. There is a lack of evidence concerning the effectiveness of school-based obesity prevention programs targeting overall students in China. We designed a cluster randomized controlled trial (C-RCT) to evaluate the effectiveness of a school-based comprehensive lifestyle intervention among Chinese kids against obesity (CLICK-Obesity) in 8 urban primary schools in Nanjing City, China. When designing the C-RCT we considered the unique cultural, academic and traditional aspects of Mainland China, as well as the urgent need for this type of intervention. This report presents the methodology used in this C-RCT.

## Methods

### Study design and recruitment of participants

This school-based C-RCT has being conducted from May 2010 to December 2013 in Nanjing, a large city in eastern China which had a registered population of more than 6.2 million in 2009. The intervention took place within Jianye, an urban district of Nanjing. In 2009, there were 13 primary schools in Jianye district, among which eight schools were randomly selected as target schools and randomly assigned to either the control or intervention group (four schools in each group). All the fourth graders in each of the selected schools were invited to participate in the study. Written informed consent was obtained from both the schools and parents/students’ guardians. Figure 1 presents the study mapping process. Although the entire project was designed to be three and half a year, the field intervention was planned to be implemented among intervention group within one academic year from May 2010 to April 2011, while three surveys were scheduled to collect data from all participants (both intervention and control groups) in this study: (1) The first survey was conducted in May 2010 to collect baseline data; (2) The second was in May 2011 to gather data for evaluating the intervention effectiveness immediately after field intervention; (3) The third will be in May 2012 to collect data also for assessing the intervention effectiveness one-year later after field intervention. This study was approved by the academic and ethical committee of Nanjing Municipal Center for Disease Control and Prevention.

**Figure 1 F1:**
[figure not shown]
The Study Mapping Process of CLICK-Obesity Program.

### The intervention

#### The theoretical basis

The intervention component of our CLICK-Obesity study was developed based on the HEALTH-KIDS Study conducted by one of our team members in Chicago [17], but related changes were made to adapt to the situation in Nanjing in China. The HEALTH-KIDS intervention was designed based on several behavioral theories including the Theory of Triadic Influence (TTI) [28] and the Comprehensive School Health Program Model (CSHPM) by the United States of America Center for Disease Control (US CDC) [29], Briefly, the TTI theory was intended to account for factors that had direct and indirect effects on behavior and both new behaviors and regular behaviors, while the CSHPM model, a strategy designed for school-based behavior intervention projects, was recommended by the US CDC for school-based intervention programs to promote life-long healthy eating and physical activity habits.

#### Intervention components and implementation

Students attending schools allocated to the intervention group received the field intervention program between May 2010 and April 2011, while students in the control group followed their usual health and physical education curriculum. As shown in Figure 2, the intervention consists of four components: a) classroom curriculum (including physical education and healthy diet education), b) school environment support, c) family involvement, and d) fun programs/events. The intervention was developed after taking full consideration of Chinese cultural and familial tradition, social convention, and the current primary education and examination system. In China, familial expectations usually lead to Chinese students being encouraged to spend a relatively large amount of time in academic studies, and to achieve highly competitive exam scores, and schools primarily define their quality and reputation by their students’ academic performance. These cultural and social contexts must be considered when designing and implementing any school-based lifestyle and behavioral intervention project in Mainland China.

**Figure 2 F2:**
[figure not shown]
The Field Intervention Framework of CLICK-Obesity Program.

All developed intervention components were integrated into the regular academic schedule of each school. For example, all schools in Mainland China are required by the educational authority to provide health-related curriculum each semester; we encouraged the intervention schools to use our curricula to meet this requirement (which all schools in the intervention group did). Another example is that all schools in China have a regular class session where parents/guardians are invited to attend. We encouraged the intervention schools to use these sessions (parent class) to provide parents/guardians with healthy diet and active lifestyle messages to prevent obesity among children and advice to help their children eat healthy food and engage in more physical activity after school.

a) Classroom curriculumThe classroom curriculum was designed to disseminate knowledge and skills to promote individual healthy eating behaviors and to increase inside-/outside-school physical activity. One 30-minute lesson was delivered by regular classroom teachers each month for one academic year (8 months) for the 4^th^ graders in the intervention group. All teachers were trained and provided with the same teaching materials to present for students. Members from our program team attended each class and sat in the back of the classroom to view each curriculum presentation lesson.The curriculum consists of two education modules: one focused on nutrition and the other on physical activity. The nutrition module aimed to help students reduce unnecessarily excessive energy intake, while the physical activity module focused on increasing energy expenditure. The nutrition module included an introduction to types of foods, and energy contained in different foods and practical advice on how to eat healthily on a daily basis. Students were shown what high-dense-energy foods are, for example Western snacks, soft-drinks and deep-fried foods. They were encouraged to consume low-dense-energy foods, such as vegetables and tofu. They were also offered tips on how to eat healthily, e.g., chewing thoroughly, and reducing fat intake by consuming meat without skin. The physical activity module encouraged students to engage in sufficient physical activity and to reduce screen-time. Students were also encouraged to do exercises inside or outside of the classroom during recess, and to walk to and from school.

b) School environmental supportSchool environment can be critical to helping students make desirable health-related behavioral changes and maintain a healthy lifestyle. Brief health-related messages and posters were presented in all intervention schools, in locations such as inside the classroom, gymnasium, playground, and cafeteria. The messages and posters were updated monthly according to scheduled intervention themes. Furthermore, posters made by students were posted on rear blackboards in classrooms in intervention schools. The posters promoted healthy eating and physically active behaviors. Selected examples of the blackboard poster titles included: “To be physically active is a good and wise way to reject obesity”, “Healthy eating can keep obesity away” and “Indulging in foods can guarantee your bad health”. Posters were updated by students monthly.

c) Family involvementParents/guardians are the gatekeepers for their children’s food choices, and they also serve as role models for their children by practicing and reinforcing healthy lifestyle choices [17,30]. Family involvement was developed to introduce families to the CLICK-Obesity intervention and to assist them to create a supportive environment for helping children change unhealthy behaviors and increase healthy eating and physical activity. The family involvement component included parents/guardians health class at school, in which they were invited to participate in an educational program twice per semester to learn appropriate strategies to advance healthy lifestyle choices against obesity. Families were given the opportunity to discuss practical aspects of the CLICK-Obesity program and to extend their knowledge on healthy lifestyle and eating behaviors. The curriculum designed for parents/guardians were organized by class teachers but presented by our team members each time, unlike the class curriculum which was presented to students by classroom teachers. After school family events were also offered, these included parent–child interactive home assignments, such as identifying high-dense-energy home foods, and practicing to measure body weight and height and to calculate body mass index.

d) Fun programs/events

(i) Presentation competition. Three competitions (picture painting, short paper writing and stage drama) were held in two semesters regarding (a) obesity and its associated risk to health, and (b) healthy lifestyle and behaviors against obesity in daily life. Students were encouraged to tell their own stories about healthy diet and physical activity behaviors. Picture painting, focusing on healthy lifestyle choices, and paper writing activities, focusing on healthy body weight, were implemented during the first semester. A stage drama, presenting how to keep a healthy body weight through healthy lifestyle and behaviors in daily life, was required to be presented by a classmate-team (at least two members) in the second semester. Six winners from each class were selected for each picture painting and paper writing competition, while one winner in each class was selected for stage drama show by a 7-member assessment panel, which including external experts (from the local Center for Disease Control and students’ health-care institute), teachers and classmates.

(ii) ‘No unhealthy snack week’. Students were encouraged to consume no high-dense-energy snacks for a week in early March 2011, and to take regular meals and fruits at home and school. A specific card designed to reinforce positive attitude and healthy practice was delivered to each participant in order to record his/her weekly snack consumption.

(iii) ‘No TV week’. In a selected week in late March 2011, we designed a program to encourage students to turn off TV at home and reduce computer-use to a minimal level at home and school. The parents/guardians received leaflets encouraging them to help their children do so at home. Students were also asked to report their daily screen-time during the week.

(iv) ‘No soft drink week’. In a week in late April 2010, students were advised to refrain from consuming soft-drinks and to drink pure fresh water instead. They were also required to record their soft drink consumption during that week.

### Data collection and measurement of key study variables

Anthropometric measures and interviewer-assisted questionnaire surveys were conducted at baseline (May, 2010), the first follow-up (May, 2011) and will be at the end-point follow-up (May, 2012). A structured 39-item questionnaire was designed to collect information on students' and their parents' socio-demographic characteristics, knowledge regarding obesity and its risk factors, intake of meat and vegetables/fruits, consumption of high-dense-energy snacks and soft-drinks, and physical activity. Additional information on lifestyle/behavior change was collected at the first follow-up survey. As part of the baseline survey parents/guardians completed a short questionnaire focusing on their families socio-demographic characteristics. Information collected included parental educational attainment, and family size and structure.

Trained Nanjing CDC research team members, each of whom had a university degree in a health-related discipline, conducted the physical examination and the survey in the classroom setting. Prior to the survey research staff clearly explained to the students the survey procedure and the questionnaire item by item. Students were then invited to self-complete the questionnaire in the classroom. On average, the questionnaire survey took approximately 20 minutes to complete. A school teacher supervised and assisted the survey procedure in each class.

(1) Anthropometry: Students’ body weight, height and waist circumference (WC) were measured by trained research staff. Students, wearing light indoor clothing and without shoes, had their weight measured to the nearest 0.1 kilograms using a beam balance scale, and height measured to the nearest 0.01 meter using a stadiometer (Wuxi Weight Factory, Wuxi, Jiangsu, China). Using a non-elastic flexible tape, WC was measured to the nearest 0.1 centimeter at the midpoint between the costal inferior and iliac crest. Each of these anthropometric variables was measured twice and the mean of the two readings for each were used in our analysis.Overweight was defined as BMI between 85^th^ and 95^th^ percentile value, while obesity as BMI ≥ 95^th^ for age- and sex-specific reference data according to the recommendation for Chinese children by the Group of China Obesity Task Force [31]. In this Report we use the term ‘excess body weight’ (EBW) to describe being overweight or obese (BMI ≥ 85^th^ percentile value).

(2) Study variables collected in the questionnaire survey

(a) Socio-demographic characteristics: These included student’s age, gender, grade, school, ethnicity, parental educational attainment (classified into 3 subgroups: ≤9 yrs, >9 but ≤ 12 yrs, and ≥13 yrs), and family size and structure.

(b) Obesity-related knowledge: A series of questions were asked regarding knowledge about obesity and its related behavioral risk factors and long-term influence of childhood obesity. All these variables were categorized as “Yes” or “No or do not know”. For example, the question about information on screen time use was “Do you think spending prolonged time in viewing TV or using the computer can result in excess body weight?”

(c) Dietary intake: Items from a specifically validated Frequency Food Questionnaire (FFQ) were selected to gather information on dietary consumption including meat, vegetable/fruit, snack and soft-drinks [32]. All variables will be categorized into tertiles for our analysis.

(d) Physical activity and sedentary behavior: These were assessed using the Chinese version of the International Physical Activity Questionnaire (CHN-IPAQ) [33]. We will calculate moderate physical activity (MPA) time based on time spent in jogging and doubled the time in ball playing and swimming. Time spent on homework, sleep and commuting to/from school were also collected.

(e) Behavior change: Students were asked questions on changes in lifestyle and behavior (dietary intake, physical activity and sedentary behavior) at first follow-up compared to the baseline survey. Responses were recorded on a 5-point Likert scale (increasing a lot, increasing a little, no change, decreasing a little, and decreasing a lot).

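### A school teacher assists the self-completed questionnaire in every class, and in intervention schools classroom teachers gave the lessons; the two roles are not kept apart, which may add arm-dependent reporting bias to the secondary outcomes

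*Protocol article*

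**What the plan says.** The Data collection section of the Protocol article describes who was in the room for the questionnaire. Trained research team members from the Nanjing CDC "conducted the physical examination and the survey in the classroom setting" and explained the items beforehand. For the response itself, "Students were then invited to self-complete the questionnaire in the classroom". The section then adds: "A school teacher supervised and assisted the survey procedure in each class". It makes no distinction between intervention and control schools.

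The Intervention components and implementation section describes who taught. Under Classroom curriculum: "One 30-minute lesson was delivered by regular classroom teachers each month", over an academic year of 8 months, with training and common materials. Under Family involvement the same is said again, by contrast with the parents' sessions: "unlike the class curriculum which was presented to students by classroom teachers". Control schools kept their usual health and physical education curriculum.

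The abstract says that the "secondary outcomes were behaviour and behavioural determinants". The questionnaire supplies these: obesity knowledge, meat, vegetables and fruit, snacks, soft drinks, physical activity and, at the first follow-up, self-rated behaviour change.

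**The concern.** The written survey procedure is the same in both arms, but the teacher's relation to the content is not. In an intervention school the teacher in the room may be one who spent the year teaching that snacks, soft drinks and screen time should be cut. In a control school no teacher delivered the study lessons. Pupils in the intervention arm may then lean towards the taught answer because of who is present or helping, with no matching pull in the control arm.

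The behavioural secondary outcomes are at stake. If reporting shifts in one arm only, part of an apparent change in behaviour could be a change in reporting. The May 2011 survey has been done, but the article places the May 2012 survey in the future, so that one can still be protected.

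**Working it through.** The article gives no figure on this point, so the check is a comparison of its sections.

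1. **Teacher's role at the survey.** Data collection: a school teacher supervises and assists in each class, in both arms. The object of the assistance is the survey procedure. Help with individual answers is neither stated nor excluded.
2. **Teacher's role in the intervention.** Classroom curriculum and Family involvement: classroom teachers gave the lessons, in intervention schools only. Class teachers there also organised the parents' sessions, and teachers sat on the panel that chose competition winners (Fun programs/events).
3. **Link between the two.** No section says that the teacher at the survey is, or is not, the one who taught that class. The overlap is possible and unverified.
4. **Overlap of content.** The lessons covered energy-dense foods, soft drinks, vegetables, physical activity and screen time. The questionnaire asks about these topics. In the one knowledge question that the article prints, on screen time, an affirmative answer is the one in line with the lessons.
5. **Does the analysis remove it?** Statistical analysis: multilevel models compare post-test values corrected for pre-test measurements. Baseline was May 2010, at the start of the programme. Pre-test correction deals with stable differences between classes or teachers. It does not remove a reporting shift created by the lessons, because that shift is absent at baseline. The self-rated change item is asked at first follow-up about change since baseline, so it has no pre-test value.
6. **Which outcomes are exposed?** Only those from the questionnaire. Weight, height and waist circumference were measured by trained research staff, so BMI, on which the Power calculation rests, is outside the concern.

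**Illustration on assumed inputs only.** Assume a binary item with 30% in the control arm, a pure reporting shift d in the intervention arm, 600 pupils per arm (1200/2) and the design effect of 1.75. The 30% and d are invented. The 1.75 comes from the BMI calculation and is borrowed.

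- Variance = 1.75 × [0.30 × 0.70 + (0.30 + d)(0.70 − d)] / 600; z = d / √variance; chance of a significant result in favour of the intervention at two-sided 0.05 ≈ Φ(z − 1.96).
- d = 0.02: variance 0.001247, z = 0.57, about 8%.
- d = 0.05: variance 0.001276, z = 1.40, about 29%.
- d = 0.10: variance 0.001313, z = 2.76, about 79%.
- With a t reference on 6 degrees of freedom (8 schools − 2), the last two become about 22% and 64%.

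The spread follows from the assumed d. It shows how a bias of given size would act. It is no evidence that such a bias exists, and the verdict does not use it.

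**The case against.** The strongest reply is that the decisive link is not in the text. The article speaks of a school teacher, not of the teacher who gave the lessons, and of assisting a procedure. Research staff ran the survey and explained it, and pupils filled it in themselves. A teacher who kept order and handed out forms fits this wording, and an article may leave such field detail to a manual. All of that stands. A reader might infer that pupils reported to the person who taught them, or that teachers helped with answers. The document supports neither.

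A reader might also infer that every secondary outcome is biased in favour of the intervention. The direction towards taught answers is plausible, but it is not established for every item. For knowledge items, giving the taught answer is largely what the item is meant to capture.

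Third, pupils had lessons, posters, competitions and themed weeks and could not be blinded, so some desirability bias would be present whoever stood in the room. This stands too: changing the teacher's role reduces one source and does not cure self-report. It would equally be too much to infer that research staff compounded the problem. Of the lessons the article says "Members from our program team attended each class and sat in the back of the classroom", but not that these people later ran the survey.

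What the reply does not remove is that the article does state a procedure, and that procedure lets staff involved in the intervention assist with self-reported outcomes on the taught topics, in one arm only.

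**Conclusion.** The point holds as a possible, avoidable source of differential reporting in the questionnaire-based secondary outcomes. It is not a demonstrated bias or a contradiction in the article. It rests on two stated facts, teacher assistance at the survey and teacher delivery of the lessons, and on one open question: whether the same people did both, or helped with or saw answers. The size is unknown. The BMI comparison is not touched. The point deserves action because the remedy is nearly free and one survey is still to come.

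**What to change.** In Data collection and measurement of key study variables, specify for May 2012, identically for both arms: any teacher present only keeps order; the teacher does not help with or see answers; where possible the teacher did not give the CLICK-Obesity lessons to that class; research staff alone answer pupils' questions. For May 2011, record who assisted in each class if this is still known, and report the self-reported results of that survey with this caveat.

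Cost: one survey instruction and, where possible, an exchange of teachers between classes within a school, with some rescheduling. No extra staff are needed, since research staff already run the survey. The downside is that conditions differ slightly between May 2011 and May 2012, which should be mentioned when the two follow-ups are compared.

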### Statistical analysis

Descriptive statistics were calculated. Between group difference was examined for treatment assignment and overweight status. Differences were tested using independent t-tests for continuous variables (eg, BMI) and chi-square tests for categorical variables (eg, overweight, lifestyle factors and obesity related knowledge). Multilevel regression models will be used to test for post-test group differences on the main outcome variables corrected for pre-test measurements. Data will be double entered and cleaned with EpiData 3.0 (The Epidata Association, Odense, Denmark), and managed and analyzed using SPSS 13.0 (SPSS, Chicago, Illinois). P < 0.05 is used to assess statistical significance.

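### Dietary secondary outcomes are committed to analysis as tertiles, which loses precision, coarsens the baseline correction and leaves no effect in intake units

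*Protocol article*

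**What the plan says.** The dietary items come from a validated food-frequency questionnaire and "were selected to gather information on dietary consumption including meat, vegetable/fruit, snack and soft-drinks" (Protocol article, Data collection and measurement of key study variables, item (c)). The same item fixes how they are handled: "All variables will be categorized into tertiles for our analysis". No ungrouped analysis is described, and the source of the cut-points is not given.

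The Abstract sets the rank of these outcomes: "The primary study outcome was body composition, and secondary outcomes were behaviour and behavioural determinants". The Statistical analysis section names two relevant tools. One is "chi-square tests for categorical variables (eg, overweight, lifestyle factors and obesity related knowledge"), described in the past tense. The other is prospective: "Multilevel regression models will be used to test for post-test group differences on the main outcome variables corrected for pre-test measurements". The surveys "were conducted at baseline (May, 2010), the first follow-up (May, 2011) and will be at the end-point follow-up (May, 2012").

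**The concern.** The tertile rule is a stated analysis choice that covers every dietary variable. It is not a detail left for an analysis plan to fill in. Diet is one of the routes by which the programme is meant to work: the nutrition module, the snack week and the soft-drink week all aim at it.

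Three things are at stake:

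- **Precision.** Pupils within the same third are treated as identical, so part of a real difference between arms is lost.
- **Baseline correction.** If the May 2010 value is also held as a third, it explains less of the follow-up value than the recorded frequency would.
- **Interpretation.** A shift between sample thirds cannot be stated as servings or occasions per week, which is what someone planning a later programme would want.

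**Working it through.** **The plan's own figures.** The article gives no power or precision figure for diet. The only clustering figures are in Power calculation, for BMI: 150 pupils per school, ICC 0.005, design effect 1.75. The design effect reproduces: 1 + (150 − 1) × 0.005 = 1.745. Nothing below rests on the BMI sample size itself.

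**Assumptions not in the article.** A roughly normal intake variable, a small shift between arms, a two-sided 5% test, and the BMI ICC carried over to diet.

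**Step 1: independent pupils.** The tertile cut-points of a standard normal are ±0.431, where the density is 0.3636. The efficiency of scores −1, 0, 1 relative to the ungrouped variable is

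(2 × 0.3636)² / (2/3) = 0.793, a loss of 20.7%.

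**Step 2: schools of 150.** A school effect is also a shift in location, so scoring in thirds shrinks it along with the treatment effect. The ICC on the tertile scale becomes about 0.793 × 0.005. The design effect there is 1 + 149 × 0.793 × 0.005 = 1.591. Relative efficiency is

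0.793 × 1.745 / 1.591 = 0.87, a loss of about 13%.

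**Step 3: power.** A test with 80% power has noncentrality (1.960 + 0.842)² = 7.85.

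| Setting | Noncentrality | Power, 1-df trend test | Power, 2-df unordered chi-square |
|---|---|---|---|
| Independent pupils | 7.85 × 0.793 = 6.23 | 70% | 60% |
| ICC 0.005, 150 per school | 7.85 × 0.870 = 6.83 | 74% | 64% |
| ICC 0.02 (assumed), 150 per school | 7.85 × 0.939 = 7.37 | 77% | 68% |

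The ICC 0.02 row uses 0.793 × 3.98 / 3.364 = 0.939. In the clustered rows the 2-df column supposes a chi-square corrected for clustering.

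**Step 4: baseline correction.** With both surveys held as tertiles and independent pupils, simulated efficiency relative to the ungrouped adjusted analysis is 0.74 at an assumed correlation of 0.4 and 0.67 at 0.6. Both are below the 0.793 of Step 1, so adjustment adds to the cost of grouping.

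**Step 5: other distributions (independent pupils).** Against full likelihood, tertiles keep 0.889 (logistic), 0.902 (t with 5 df) or 0.667 (Laplace), a loss of 10% to 33%. Against a t-test on raw lognormal data the ratio is 0.90 at log-SD 0.5 and 1.36 at log-SD 1.0. With strong skew, tertiles can therefore beat an untransformed t-test.

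**Step 6: cut-points.** Suppose both arms fall by 0.5 SD. With May 2010 cut-points both show 53/30/18%. With cut-points redrawn on the pooled sample at each survey both show 33/33/33%, and the fall disappears. If control falls 0.5 SD and intervention 0.8 SD, redrawn cut-points still show the contrast between arms: 28/33/39% against 39/33/28%.

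**The case against.** The case for leaving the plan alone has several parts.

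- **The loss is modest.** Clustering dilutes it to about 13% at the stated ICC, and to about 6% if the ICC for diet were 0.02. This stands, and the estimate here allows for it.
- **The distribution is unknown.** The items may be skewed or already recorded in frequency classes, in which case there may be no continuous variable to recover. This also stands. It makes the size uncertain and shapes the remedy, but it does not favour regrouping recorded classes into thirds.
- **The outcomes are secondary.** They are self-reported, and tertiles do not by themselves inflate the type I error. Agreed.

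Three stronger readings are tempting, and the article does not support them.

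- A reader might infer that the dietary effect will be tested by a 2-df chi-square. That sentence is in the past tense, also covers comparisons by overweight status, and may describe baseline tables. The prospective multilevel model may extend to diet. The chi-square column is therefore conditional.
- A reader might infer that tertiles rule out correction for the pre-test value. They do not: an ordinal multilevel model can carry the baseline category. They coarsen the correction.
- A reader might infer that tertiles hide change over time. That follows only if the cut-points are redrawn at each survey, which the article does not say, and the contrast between arms survives even then.

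The separate change item does not fill the gap. "Responses were recorded on a 5-point Likert scale", but it is a recalled direction of change, described only for the first follow-up, with no amount of intake.

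**Conclusion.** The point holds as one of efficiency and interpretation for secondary outcomes. The article commits all dietary variables to tertiles, and the choice buys nothing that a model of the recorded frequencies could not provide. The best single estimate of the cost is an efficiency of about 0.87, or about 74% power where the ungrouped analysis has 80%. It rests on approximate normality, on an ICC of 0.005 applying to diet, and on a test that uses the order of the tertiles. For independent pupils the efficiency is 0.79. It would be lower with an unordered chi-square, and it could be better or worse under other distributions. The inability to report an intake difference does not depend on any of these assumptions. The primary BMI analysis is not touched.

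**What to change.** Replace the tertile sentence with a rule to analyse each intake on the scale on which it was recorded:

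- a multilevel model with a school random effect and the May 2010 value as covariate;
- a log or rank transformation where the item is skewed;
- an ordinal multilevel model where the item was recorded in classes.

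If tertiles are kept for display, take the cut-points once from the pooled May 2010 distribution and use them at all three surveys.

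No new data are needed. The cost is some extra modelling work, plus a choice of transformation for skewed items, which should be fixed before the follow-up data are compared by arm. An effect on a log or rank scale also needs a sentence of explanation when reported.
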